### Control group: overview

#### Control group 1

Participants will receive classroom teaching once a week for 100 min each time. The total time is the same as the time required by the AIDS Fighter · Health Defense intervention group 1. A regular teacher will conduct AIDS prevention classroom education on a fixed day each week and the content of the lecture is consistent with the knowledge in the game.

#### Control group 2

Participants will be added to the QQ chat group (one of the most popular social tools in China), and the same educational resources as the “knowledge corner” in AIDS Fighter · Health Defense will be uploaded to the QQ group. Participants will then be reminded to learn the knowledge by themselves daily. But there are no gamification elements, such as barriers, points ranking, answering questions, rewards, etc.

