#### Randomization and allocation concealment

Opaque envelopes will be prepared for randomization. In 580 envelopes, each will contain a note with the words “ AIDS Fighter · Health Defense Intervention Group 1” or “ AIDS Fighter · Health Defense Intervention Group 2” or “Control Group 1” or “Control Group 2” (145 envelopes per group). Participants will be randomized to select an envelope, then assigned to the corresponding group according to the information on the envelope. The data analysts are blinded to the allocation.

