### Data management and statistical analysis

All data will be directly recorded in the online database (www.wjx.cn, Ranxing information technology co., Ltd., Changsha, China). The database system automatically saves the data and ensures the safety, integrity and consistency of the data. The web server is hosted in Alibaba Cloud (Alibaba Group, Hangzhou, China) and is protected by a corporate firewall, while a daily backup mechanism can ensure data security. Data has multi-level permission settings and password protection to ensure data security. In statistical analysis, general statistical analysis will be carried out by using standard statistical software and professional statistical software.

Analysis of Variance (ANOVA) will be used to find out whether there have differences between the AIDS Fighter · Health Defense intervention groups and the control groups in AIDS-related knowledge scores and attitude scores after the intervention of four weeks. Repeated Measures ANOVA will be used to see whether there have differences on the incidence of AIDS-related behaviors followed up for three and six months after the intervention in four arms. Intention-to-treat analysis will be used to account for the influence of attrition. The difference was statistically significant when *P* ≤ 0. 05.

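### Control group 1 is taught in a classroom but the planned ANOVA assumes independent participants; if outcomes correlate within a class, standard errors for contrasts with that arm are too small

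*Protocol article*

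**What the plan says.** All places are in the Protocol article.

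- **Unit of randomisation** (Randomization and allocation concealment): individuals draw envelopes. "Participants will be randomized to select an envelope, then assigned to the corresponding group according to the information on the envelope", with "145 envelopes per group".
- **Delivery in control group 1** (Control group: overview): "Participants will receive classroom teaching once a week for 100 min each time". "A regular teacher will conduct AIDS prevention classroom education on a fixed day each week". The number of classes, the class size and the number of teachers are not stated.
- **Delivery in control group 2** (same section): "Participants will be added to the QQ chat group", where materials are posted. "Participants will then be reminded to learn the knowledge by themselves daily". The Discussion calls this arm autonomous learning.
- **Delivery in the game arms** (Intervention group: overview): each participant uses the game, with no teacher or shared session.
- **Analysis** (Data management and statistical analysis): "Analysis of Variance (ANOVA) will be used to find out whether there have differences between" the "intervention groups and the control groups in AIDS-related knowledge scores and attitude scores after the intervention of four weeks". Behaviours at three and six months get repeated measures ANOVA. Neither sentence mentions class, teacher or chat group.
- **Sample size** (Recruitment): 131 per group for 80% power, raised to 145 per group and 580 in total for 10% attrition. No design effect is mentioned.

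**The concern.** This is an individually randomised trial in which at least one arm is delivered to groups, that is, a partially nested design. Randomising individuals balances pre-existing differences between arms. It does not remove correlation that arises afterwards, when students share a teacher, a session and classmates for four weeks. The primary outcomes include a 45-item knowledge test on the taught material, so a class effect is plausible.

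ANOVA as named assigns each of the 131 classroom participants the full information of an independent observation. If the within-class correlation is positive, the classroom mean is less precise than ANOVA reports. The contrasts at stake are each game arm against classroom teaching, the pooled intervention-versus-control comparison (hypothesis 2), and classroom against QQ (hypothesis 3). For these, confidence intervals would be too narrow and P values too small. The Discussion gives comparison with classroom teaching as one purpose of the four-arm design.

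**Working it through.** **The plan's own figures.** 131 × 1.10 = 144.1, rounded up to 145, and 4 × 145 = 580, so these agree with the text. (Dividing, 131/0.90 = 145.6, would give 146; the difference is trivial.) The 131 cannot be reproduced, because no effect size, SD or test is given. Read backwards as a two-sided 5% comparison of two independent arms with 80% power, it implies a standardised difference d = (1.96 + 0.84) × √(2/131) ≈ 0.346.

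**Inputs.** From the article: 131 analysed per arm, equal allocation, significance level 0.05 (two-sided assumed). Assumed, because the article gives neither: class size m = 30 and ICC 0.01, 0.02, 0.05 or 0.10. The calculation clusters the classroom arm only.

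**Formulas.**
- Design effect in the classroom arm: DE = 1 + (m − 1) × ICC.
- One game arm versus classroom: true variance / ANOVA variance = (1 + DE)/2.
- Two game arms pooled versus two control arms pooled: (1 + 1 + 1 + DE)/4 = (3 + DE)/4.
- True error of a nominal 5% test: 2 × [1 − Φ(1.96/√inflation)].
- Large-sample power of a valid test, one game arm versus classroom: Φ(0.346/√((1 + DE)/131) − 1.96).

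Example for ICC 0.05: DE = 1 + 29 × 0.05 = 2.45. Inflation = (1 + 2.45)/2 = 1.725 and √1.725 = 1.31. Then 1.96/1.313 = 1.49, and the true error is 13.6%.

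| ICC | DE | SE ratio, one game arm vs classroom | True error | SE ratio, pooled contrast | True error | Power of valid test, one game arm vs classroom |
|---|---|---|---|---|---|---|
| 0 | 1.00 | 1.00 | 5.0% | 1.00 | 5.0% | 80% |
| 0.01 | 1.29 | 1.07 | 6.7% | 1.04 | 5.8% | 74.5% |
| 0.02 | 1.58 | 1.14 | 8.4% | 1.07 | 6.7% | 69.4% |
| 0.05 | 2.45 | 1.31 | 13.6% | 1.17 | 9.3% | 56.9% |
| 0.10 | 3.90 | 1.57 | 21% | 1.31 | 13.6% | 43.2% |

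**Sensitivity to class size**, one game arm versus classroom, ICC 0.01 to 0.05: classes of 20 give 6.1% to 10.7%, and classes of 45 give 7.6% to 17.6%.

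**Check of the approximation.** Simulating the four-arm ANOVA with pooled error, 131 per arm and four classes in the classroom arm, the one-arm contrast rejects at about 7% for ICC 0.01, rising to about 22% for ICC 0.10. The two-arm formula is therefore adequate.

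**Sample size.** Restoring 80% power for one game arm versus classroom needs 131 × (1 + DE)/2 per arm before attrition: 150, 169, 226 or 321 for the four ICCs.

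**Number of classes.** 131/30 = 4.4 and 145/30 = 4.8, so about 4 to 5 classes. The between-class variance would be poorly estimated, and true power would fall below the large-sample values in the table.

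**The case against.** **A condensed article names only a method family.** A fuller plan could add a class effect, and the article does not say that class is ignored. That is fair, and it rules out saying the final analysis will be wrong. But the point does not rest on silence alone: the named method assumes independence. Part of the remedy is also design (how many classes, who is in which, whether class is recorded), and an analysis plan written later cannot supply it.

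**The size is unknown.** This stands. Class size, number of classes and ICC are all assumed. The claim is conditional on a positive ICC.

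**The single-arm contrast gives the larger inflation.** This also stands. The analysis section and hypothesis 2 compare intervention groups with control groups, and a pooled contrast inflates less. Both contrasts are therefore shown.

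Four stronger readings are tempting, and the documents do not support them.

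- *The QQ arm has the same problem.* Its members share a chat group, but they are told to study alone and no group teaching is described. Correlation there is possible but probably weaker. Hypothesis 3 is affected mainly through its classroom side.
- *Omitting school is part of the fault.* Individuals are randomised to all arms, so leaving out school does not make the standard errors of arm contrasts too small. A school term is optional, for precision.
- *One class of about 131 would give an error of 13% to 34%.* The formula yields 12.7% to 34.2% for ICC 0.01 to 0.05, but only for inference beyond that class. With one class the class effect is confounded with the arm. That is a limit on interpretation, which no cluster term repairs.
- *The game arms are strictly independent.* Friends' points are visible and group 1 rewards depend on rank, so some peer links exist. They are not group delivery, but a model with random effects only in the classroom arm assumes them negligible.

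**Conclusion.** The concern holds in conditional form. Individual randomisation, classroom delivery in control group 1 and plain ANOVA are all stated. Followed as written, any positive within-class correlation makes the standard errors of contrasts involving the classroom arm too small. For assumed classes of 30 and ICC 0.01 to 0.10, the true error of a nominal 5% test is about 6.7% to 21% for one game arm versus classroom, and about 5.8% to 13.6% for the pooled contrast. At ICC 0 there is none. The comparison of the two game arms (hypothesis 1) is not touched by classroom clustering.

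A reader might infer that the reported standard errors are certain to be wrong by a known amount. The article does not support that, because it gives neither the class structure nor an ICC. Its singular wording for the teacher leaves open that there is only one, in which case the issue is confounding of teacher with teaching method. The point should be acted on before teaching starts, but it does not invalidate the design.

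**What to change.** - **Design.** State the number and size of classes and the number of teachers. Teach control group 1 in several fixed classes and record class and teacher ID. Record QQ group ID if there is more than one group.
- **Analysis.** Replace the plain ANOVA by a partially nested mixed model with a random class effect in the classroom arm only and small-sample degrees of freedom. If there are several QQ groups, add a QQ-group effect as a sensitivity analysis. A school fixed effect may be added for precision.
- **One class or one teacher.** State that the classroom comparison is conditional on that class or teacher, since no model can separate the two effects.
- **Sample size.** State the assumed class size and ICC, and the power that remains for classroom contrasts.

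**Cost.** Recording IDs and changing the model are cheap. Organising several classes is a real logistical burden. With only about 4 to 5 classes, intervals for classroom contrasts will be wider and power for them will be below the stated 80%, unless more participants and classes are added.

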### Recruitment, randomization, and allocation concealment

#### Recruitment

Participants will be recruited through online recruitment and on-site recruitment. The sufficient statistical power to detect changes in AIDS knowledge, attitude and behaviors after the intervention are considered in sample size calculation, and131 participants are need in each group to maintain 80% statistical power. Assuming the attrition rate is 10%, the sample size of each group is determined to be 145, and the total sample size is 580.

The study site is Luzhou City, Sichuan Province, China. Participants will be recruited from secondary school, high school, college and university. When they agree to participate in the research and complete the follow-up measurement and informed consent form will need to be signed for confirmation. After completing the research, each participant will receive a reward of 30 RMB in cash.

#### Randomization and allocation concealment

Opaque envelopes will be prepared for randomization. In 580 envelopes, each will contain a note with the words “ AIDS Fighter · Health Defense Intervention Group 1” or “ AIDS Fighter · Health Defense Intervention Group 2” or “Control Group 1” or “Control Group 2” (145 envelopes per group). Participants will be randomized to select an envelope, then assigned to the corresponding group according to the information on the envelope. The data analysts are blinded to the allocation.

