### Study participants

This study is aimed at improving the AIDS prevention capabilities of adolescent students. The inclusion criteria are: 1) Students aged 15–24 years; 2) Participants have clear consciousness, no mental disorders, and able to read and express themselves; 3) Participants were informed about the study and voluntarily participated in the study (< 16 years old requires the consent of the guardian). Those who are diagnosed as HIV positive will be excluded from the study.

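### Participants pick their own envelope from a common pool, so there is no preset order against which a redraw or swap could be checked

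*Protocol article*

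**What the plan says.** Under Randomization and allocation concealment, the Protocol article states: "Opaque envelopes will be prepared for randomization". There are 580 of them, with "145 envelopes per group", and each contains a note naming one of the four arms. The assignment step is: "Participants will be randomized to select an envelope, then assigned to the corresponding group according to the information on the envelope". The only blinding mentioned there is that of the data analysts. The section does not mention a generated sequence, sealing, numbering, a custodian or a record of the draw. It does not mention strata or blocks either.

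Under Recruitment: "Participants will be recruited through online recruitment and on-site recruitment", and "Participants will be recruited from secondary school, high school, college and university". The eligible population is "Students aged 15–24 years", and the study site is one city.

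The overviews of the intervention and control groups show how different the arms are to a participant:
- **Intervention group 1:** the game with required playing time, and 50 or 20 RMB by points rank.
- **Intervention group 2:** the game with no required time and no incentives.
- **Control group 1:** a 100-minute class each week.
- **Control group 2:** a chat group with the same material and no game elements.

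Every participant who completes the study receives 30 RMB.

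**The concern.** Allocation concealment has to do two things. It must hide the next assignment until a person is committed to the trial, and it must make the assignment hard to change once it is seen. Opaque envelopes serve the first purpose. The second needs a fixed order, so that anyone can later establish which envelope belonged to which participant. When the participant's own pick is the allocation, that order does not exist.

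Two breaches would then be hard to see: opening an envelope, putting it back and drawing another, or exchanging notes with another participant. There is a motive for both, because the note names the arm and the arms differ in effort, entertainment and cash.

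A trade of this kind would sort participants by motivation. That plausibly affects knowledge and attitude scores, and adjustment for recorded baseline variables would not fully remove it. Blinded analysts could not detect it. Intention-to-treat analysis would not repair it, because it takes the recorded assignment as given.

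**Working it through.** **1. The plan's own counts.** The Recruitment section gives 131 evaluable participants per arm and 10% attrition. Then 131 × 1.1 = 144.1, rounded up to 145, and 131 / 0.9 = 145.6, rounded up to 146. The stated figure is 145. The total is 4 × 145 = 580, which matches the number of envelopes. Nothing below depends on the choice between 145 and 146.

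**2. Which breaches the fixed count would reveal.**

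| Event | Effect on the pool and arm totals | Visible at full recruitment? |
|---|---|---|
| Envelope discarded, another drawn | Pool runs one short; one arm falls below 145 | Yes, in principle |
| Envelope returned, another drawn | None | No |
| Two participants exchange notes | None | No |

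The count therefore exposes the first event and not the other two. If recruitment stops short of 580, arm totals vary by chance and the count is no longer a clear check on discards either.

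**3. Illustration of the size of a swap.** The document gives no rate of breach, so all inputs here are assumptions. Suppose 10 of 145 in intervention group 1 trade places with 10 in a control arm, and the two sets of ten differ by 0.5 SD in the outcome. Each arm mean moves by 10/145 × 0.5 = 0.034 SD, in opposite directions, so the arm difference shifts by 2 × 10/145 × 0.5 = 0.07 SD.

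For scale, the article gives no effect size, but 131 per arm at 80% power and two-sided 0.05 (sidedness assumed) corresponds to (1.960 + 0.842) × √(2/131) = 0.346 SD. The shift would be about a fifth of that (0.069/0.346 = 0.20). It scales in proportion to the number of swaps and to the assumed difference.

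**4. Chance imbalance in education level under an honest draw.** The mix of levels is not given, so the shares are assumptions. For a level with a 25% share, the SD of the difference between two arms is √(2 × 0.25 × 0.75 / 145) = 0.051, about 5 points. The 95% range is 1.96 × 0.051 = 0.10, about ±10 points. Simulated draws of 145 envelopes per arm (200,000 runs) gave:

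| Assumed share | SD, two given arms | P(gap > 10 points), two given arms | P(largest gap among four arms > 10 points) |
|---|---|---|---|
| 10% | 3.5 points | 0.4% | 2% |
| 25% | 5.1 points | 5% | 20% |
| 50% | 5.9 points | 9% | 32% |

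If the 25% level differs from the rest by 1 SD in knowledge (assumption), the shift in an arm difference is about 0.05 SD typically and 0.10 SD at the 95% limit. For both game arms against both control arms, 290 against 290, the 95% limit is 1.96 × √(2 × 0.25 × 0.75 / 290) = 0.07 SD.

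**The case against.** The strongest reply is that the stated procedure, carried out honestly, is sound. The arm name is hidden inside an opaque envelope, so the participant cannot choose an arm by choosing an envelope, and a blind draw from a balanced pool is proper randomization. That stands. Bias needs a breach, and the article gives no evidence that one is likely. The cash motive is also modest: 20 to 50 RMB, in one arm only, beside 30 RMB for everyone who completes.

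Three stronger readings are tempting, and the document does not support them.
- **That the envelopes are unnumbered and tampering is undetectable.** The article is silent on sealing, numbering and logging, and a condensed article may leave these to the full protocol. The fixed count would also expose some discarded envelopes.
- **That online recruits cannot draw an envelope.** The text describes a recruitment channel. The trial is in one city, consent must be signed, and any participant may be sent to a weekly class, so an in-person draw is compatible with it. How it is done is simply not explained.
- **That a single unstratified pool is an error.** The text fits one pool, but chance imbalance is not bias, is already allowed for in the test, and can be handled by adjustment in an analysis plan not shown.

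What the reply does not answer is that the free pick is stated, not omitted. Sealing or numbering the envelopes would not by itself create an order linking them to participants as long as each participant chooses among them.

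**Conclusion.** The point holds as a weakness of the stated allocation method. Participant choice from a common pool leaves no predetermined link between person and envelope, the article describes no safeguard, and a returned redraw or a swap could pass unnoticed between arms of visibly different appeal. It does not show that allocation will be subverted or that the randomization is invalid.

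The size of any selection bias cannot be derived from the document. The 0.07 SD figure illustrates ten swaps and a 0.5 SD difference, both assumed. Education imbalance is a secondary matter of precision, at about 0.05 SD typically and 0.10 SD at the 95% limit, on an assumed 25% share and an assumed 1 SD difference in knowledge. The change should be made before enrolment, because an audit trail cannot be created afterwards.

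**What to change.** Replace the free pick with a computer-generated allocation sequence, prepared and held by someone who does not recruit. Either place it in sequentially numbered, sealed, opaque envelopes, taken strictly in order, or release it centrally. Record participant ID and date before each envelope is opened. State that online recruits are allocated from the same list, and how. Envelopes are already planned, so the cost is a little list and log administration.

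Optionally, stratify by education level using blocks of randomly varying size, and include the strata in the analysis model. This reduces chance imbalance only. It means several short lists in place of one pool. Because past allocations are visible to recruiters, blocks also make some late assignments predictable unless their sizes vary. If that trade is unwelcome, a single unstratified list still resolves the main point.

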### Outcomes and data collection

The primary outcomes are AIDS-related knowledge, AIDS-related stigma attitude and AIDS-related behaviors attitude before and four weeks after the intervention. AIDS-related knowledge will be assessed through a self-made questionnaire with a total of 45 items, one point for a correct answer. The higher the score, means the more knowledge participants have learned. AIDS-related behaviors attitude will be assessed through a questionnaire with eight items, with one point for a correct answer. The higher the score, means the lower the risk of AIDS-related behaviors among participants. Five experts were invited to verify the content validity of these questionnaires, the item-level CVI (I-CVI) and the scale-level CVI (S-CVI) are both 1. 00. AIDS-related stigma attitude will be assessed through the Chinese version of Zelaya’s HIV/AIDS Stigma Scale, which was compiled by Zelaya [16], with 24 items in total, and was Sinicized by Xing Haiyan [17]. After Sinicization, the I-CVI was 0. 82 ~ 1. 00, and the S-CVI was 0. 97. Each item uses a score of 1–5. The higher the score, the more the participants’ stigma of AIDS.

Secondary outcomes are the AIDS-related behaviors followed up for three and six months after the intervention. Participants will receive cash rewards after completing the evaluation. AIDS-related behaviors will be assessed through the Questionnaire on the Health of Young Students that was issued by the Chinese Center for Disease Control and Prevention, which has 33 items and is the official questionnaire for the investigation of AIDS-related behaviors among adolescents in China. The fewer AIDS-related risk behaviors, the more the participants have gained AIDS prevention capabilities.

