## Methods/design

### Study design

Study participants will be recruited from adolescent volunteers and allocated to one of the four randomized groups after completing a baseline survey (Fig. 1) (AIDS Fighter · Health Defense intervention group 1; AIDS Fighter · Health Defense intervention group 2; control group 1; control group 2). Participants are required to complete the assessment four weeks later and three-month, six-month follow up visit after the intervention. Our hypotheses are:
There is no statistical difference between AIDS Fighter · Health Defense intervention group 1 and AIDS Fighter · Health Defense intervention group 2 in AIDS-related knowledge, stigma attitude, risk behaviors attitude and the incidence of risk behavior;Compared with adolescents in the control groups, those in the AIDS Fighter · Health Defense intervention groups will have More AIDS-related knowledge, less AIDS-related stigma and fewer AIDS-related risk behaviors.Comparison between control group 1 and control group 2, group 1 will show better effects in improving AIDS-related knowledge, attitude and behaviors.

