## Discussion

In developed countries, the focus of AIDS prevention education is on the sexual behavior of high-risk groups, but the focus of AIDS education in our study is on the AIDS-related knowledge of adolescents. The awareness rate of AIDS knowledge among the public in developed countries might be higher than China, and existing studies are mainly aimed at high-risk groups, such as men who have sex with men and adolescents who have sex without condoms [18, 19]. But in China, the awareness rate of AIDS among the public is low [20], especially adolescents in poor areas and western China [21, 22].

Adolescents are in the sexually active period are a high-risk group of HIV infection [23], the awareness rate of AIDS among them is low [24], and the HIV infection rate is high in China [25], AIDS preventive education for them is crucial. Therefore, the target of HIV prevention education in China should be the public, especially adolescents.

To meet the need of AIDS education of adolescents, the educational game “AIDS Fighter · Health Defense” was developed. As mentioned above, AIDS Fighter · Health Defense is a theory-based AIDS education game that can provide knowledge and skills to adolescents to prevent AIDS. Whether adolescents are interested in AIDS Fighter · Health Defense and insist on using it is the key to this study. If the game does not appeal to adolescents, it will not be popularized among them, nor have educational significance. To promote the use of this game by adolescents, the game is designed to be highly interactive and interesting, including gamification elements as levels, points, answering questions, rankings, and rewards. In the levels of the game, seven different organs and systems of the human body are simulated, it can vividly show the way HIV invades the human body and its performance if infected with HIV. This can not only improve the fun of the game, but also popularize the process of HIV invading the human body, which may increase users’ willingness to play the game and prevent AIDS.

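### Three unranked primary scores are each tested at P ≤ 0.05 with no success rule, so the main comparison carries up to about a 14% chance of a false positive

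*Protocol article*

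**What the plan says.** The Outcomes and data collection section defines the primary endpoint as three scores: "The primary outcomes are AIDS-related knowledge, AIDS-related stigma attitude and AIDS-related behaviors attitude before and four weeks after the intervention". The abstract names the same three. Neither place ranks them.

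For these scores the Data management and statistical analysis section says "Analysis of Variance (ANOVA) will be used to find out whether there have differences", and the comparison it goes on to name is intervention groups against control groups at four weeks. The same section closes with the only decision rule in the article: "The difference was statistically significant when *P* ≤ 0. 05".

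The Study design section lists three hypotheses:

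- Hypothesis 1 compares the two game arms and predicts equality: "There is no statistical difference between AIDS Fighter · Health Defense intervention group 1 and AIDS Fighter · Health Defense intervention group 2".
- Hypothesis 2 compares game arms with control arms and predicts that the game arms "will have More AIDS-related knowledge, less AIDS-related stigma and fewer AIDS-related risk behaviors".
- Hypothesis 3 compares the two control arms and predicts that "group 1 will show better effects in improving AIDS-related knowledge, attitude and behaviors".

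The article gives no order of testing, no division of the 5%, no adjustment, and no statement of how many primary scores must be significant.

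**The concern.** The trial is meant to answer whether the game improves AIDS prevention ability. Three scores can each answer that, each at 5%. If a single significant score is enough, the 5% level describes each test and not the conclusion drawn from the set. If all three are needed, there is no inflation, but power is lower than for any one score. These rules have different error rates and different power, and the text allows the choice between them to be made after the results are seen.

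Hypothesis 2 does not settle the matter. It names knowledge, stigma and risk behaviors. The last of these is a secondary outcome, and the third primary score, behaviors attitude, does not appear in it.

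**Working it through.** **The plan's own figure.** The article states a per-test threshold but no overall error rate, so there is no stated rate to reproduce.

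**Inputs**
- Three primary scores (Outcomes and data collection).
- Threshold 0.05 for each test (Data management and statistical analysis). Sidedness is not stated; two-sided is assumed.
- Four equal arms (Randomization and allocation concealment), with 131 per arm needed for 80% power (Recruitment).
- Correlation between the scores: not given; 0 to 0.9 assumed.

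**Step 1: intervention versus control on three scores, any one sufficient.** With every null hypothesis true and independent scores, the chance of at least one false positive is 1 − (1 − 0.05)³ = 1 − 0.857 = 14.3%. Correlated scores were simulated (100,000 replicates, four arms of 131, pooled intervention against pooled control). The table also gives the result if the ANOVA is a four-arm overall test on each score.

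| Correlation | Pooled contrast, 3 scores | Four-arm ANOVA, 3 scores |
|---|---|---|
| 0 | 14.3% | 14.3% |
| 0.3 | 13.7% | 13.9% |
| 0.5 | 12.5% | 12.8% |
| 0.9 | 8.2% | 8.6% |

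The result hardly depends on which form of ANOVA is meant.

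**Step 2: direction.** These rates count errors both ways. Counting only false results in favour of the game, where each two-sided 5% test contributes 2.5%, gives 1 − 0.975³ = 7.3% if independent, 6.4% at correlation 0.5 and 4.2% at 0.9. The benchmark is then 2.5%, so the relative inflation is about the same or slightly greater.

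**Step 3: adding hypothesis 3 on the same scores.** Six tests give 1 − 0.95⁶ = 26.5% if independent; simulated, about 23% at correlation 0.5 and about 16% at 0.9.

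**Step 4: what an adjustment costs.** The 131 cannot be reproduced, because the article gives no effect size or SD. Assume it stands for a two-arm, two-sided 5% test with 80% power. The implied standardised difference is d = (1.960 + 0.842) × √(2/131) = 0.346. Bonferroni's level, which is also Holm's first, is 0.05/3 = 0.0167, with critical value 2.394.

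- Pooled contrast, 262 against 262: 0.346/√(2/262) = 3.96, and power = Φ(3.96 − 2.394) = Φ(1.57), about 94%.
- Two single arms, 131 against 131: power = Φ(2.802 − 2.394) = Φ(0.41), about 66%.

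**The case against.** Four points can be made for the plan.

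**The rest may be in the analysis plan.** Multiplicity procedures are often specified there, and this is a condensed article. That would excuse a missing procedure. It does not remove the point, because the article itself declares three equal primary outcomes and sets the significance rule for them without qualification. An analysis plan that adjusted would have to override the published rule.

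**Hypothesis 2 joins its predictions with 'and'.** If all parts had to hold, that claim would have no inflation. The wording leans that way but is not a decision rule, and its list does not match the primary outcomes. Read literally, it covers only two primary scores, for which an any-one rule gives 1 − 0.95² = 9.75%.

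**The number of tests can be overstated.** A reader might multiply three scores by three hypotheses and infer nine primary tests and a false positive chance of about one in three (1 − 0.95⁹ = 37.0%; about 33% at correlation 0.5). The documents do not support that:
- Hypothesis 1 predicts no difference, so a significant result contradicts it and cannot be a false positive for it. Its weakness, concluding equality without a margin, is a separate matter.
- The analysis section names only intervention versus control for the primary scores.
- A figure near one half would need 18 ungated pairwise tests, which the article nowhere describes. If pairwise tests followed only a significant ANOVA, the chance of any false claim with all arms equal could not exceed that of the three overall tests, about 14%.

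**The Discussion might seem to rank knowledge first.** It says "the focus of AIDS education in our study is on the AIDS-related knowledge of adolescents". In context this contrasts the content of the education with work on high-risk groups elsewhere. It does not order the endpoints.

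The last two points limit the size of the concern. None of the four supplies the missing success rule.

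**Conclusion.** The concern holds for the main comparison. As published, one significant score out of three unranked primary scores could support the claim that the game works. On that reading the chance of at least one false positive is 12% to 14% for correlations from 0 to 0.5, and about 8% at 0.9, against a nominal 5%. It rises to at most about 26% if the two control groups are also compared on the same scores.

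These figures assume that all null hypotheses are true, that tests are two-sided, and that any one score suffices. If all three scores had to be significant, the error for this comparison would not exceed 5%; the article does not say which rule applies. This should be corrected, but it needs no change of design.

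**What to change.** State in the analysis section that the primary comparison is pooled intervention versus pooled control at four weeks, and that the three scores are tested by Holm's procedure at an overall two-sided 5%: smallest P value against 0.0167, next against 0.025, last against 0.05, stopping at the first failure. This needs no ranking of the scores.

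Two alternatives also work if fixed before any outcome data are seen: a pre-specified sequence of the three scores, or a requirement that all three be significant at 5%. In the sequence, later scores lose confirmatory status once one fails. Under the all-three rule, one weak score prevents a positive result.

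Label control group 1 versus control group 2, the other pairwise contrasts, and the three- and six-month results as supportive. Keep the no-difference hypothesis for the two game arms outside this error rate.

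The cost is wording, a stricter threshold for the smallest P value and some power. Under the assumption about the 131, the pooled contrast keeps about 94% power at the strictest Holm level. If the primary comparison were instead a single pair of arms, power at that level would be about 66%, and keeping 80% would need about 175 per arm before attrition. The choice of contrast should therefore be written down together with the adjustment.
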